#### Effectiveness trial

The effectiveness trial will be run in Victoria for practical reasons (ie, funding constraints regarding in-school data collection and professional learning sessions, and multiple ethics approvals that would be required from Departments of Education in different states/territories). Up to six Victorian special schools (up to n=3 intervention and n=3 waitlist control; out of n=61 eligible schools) will be recruited for the effectiveness trial. School staff in the intervention school will be offered at least one in-person professional development opportunity at their school. School staff will also access the *TransformUs All Abilities* training material, programme components and programme resources through the *TransformUs* website (https://transformus.com.au) and will be encouraged to use the strategies in their classrooms/school.

Intervention effectiveness will be assessed in relation to device-measured students’ physical activity and sedentary time (primary outcomes), sleep, physical literacy and cognitive functions (secondary outcomes), as well as teachers’ confidence and competence in implementing the *Transform All Abilities* programme (secondary outcomes). Teachers’ feedback on their experience of delivering the programme and the perceived barriers and facilitators to implementation will be sought with audio-recorded interviews/focus groups at the end of the trial. Additionally, at the end of the trial, we will conduct a 45 min focus group session with a small group of students at each intervention school to understand how students with disabilities view the opportunities for physical activity throughout the school day. With these discussions, we will aim to understand (1) students’ perceptions of the *TransformUs All Abilities* programme; (2) their enjoyment in relation to the programme and (3) perceived barriers and facilitators to the implementation of physical activity strategies in their schools.

The principal/nominated school leader will help to oversee the implementation of the intervention in the school. A nominated school contact/liaison will distribute information on the study for the purposes of recruiting staff and students for the evaluation and will help to coordinate the assessments when the research team visits the school.

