#### Effectiveness trial

Principals or nominated school leaders will receive an invitation for their school to participate in the effectiveness trial. After receiving informed principal consent, schools will distribute recruitment information to parents/children. Parental written/electronic consent for their child to participate in the study will be sought prior to the study commencement. In addition to the informed consent received from parents/guardians, verbal assent from students will be obtained prior to any student assessment through any communication means (eg, verbally or via alternative and augmentative communication). Allocation to intervention/wait-list control will be done pragmatically, based on schools’ preference.

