#### Effectiveness trial

For our primary outcome—ActiGraph-measured MVPA (min/day)—we are aiming to recruit a total of 134 students (intervention n=67; control n=67). Allowing for a 30% drop-out and incomplete data (accelerometer not worn for enough hours per day or days over the week), this would still give us a sufficient power to detect statistically significant differences in the primary outcome.

For data to be analysed with linear mixed models (additional details available in section ‘Data Analysis’), the fixed effects were estimated with an a priori power calculation using G*Power software. Assuming a moderate effect size (f² = 0.15), an α error probability=0.05, and power (1 – β error probability) = 0.80, and the group variable as predictor, fixed effects were estimated to require 55 observations. To account for the random effects of clustering (students in the same classroom), a design effect of 1.82 was estimated (based on a coefficient of variation of 0.15 and an average number of five students per classroom and a conservative Intraclass Correlation Coefficient value of 0.20), suggesting that 100 observations would be required (ie, 55×1.82 = 100). Accounting for 25% attrition, the final total sample size needed for the effectiveness trial is 134 participants (ie, 100 ÷ (1–0.25) = 134), from 27 classrooms (134 ÷ five students per class=27).

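### The effectiveness power calculation inflates for classrooms only, although at most three schools per arm are allocated whole, so the stated 80% power is not supported

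*Protocol article*

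**What the plan says.** **Allocation.** Under Procedures and participants (Effectiveness trial), the protocol plans "Up to six Victorian special schools (up to n=3 intervention and n=3 waitlist control; out of n=61 eligible schools"). Under Recruitment strategy (Effectiveness trial) it adds: "Allocation to intervention/wait-list control will be done pragmatically, based on" what the schools themselves prefer. The school is therefore the unit that enters an arm, and six is a maximum.

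**Sample size.** Under Sample size and power calculation (Effectiveness trial), the chain is printed in full. It starts from "Assuming a moderate effect size (f² = 0.15"), with "an α error probability=0.05" and power 0.80, group being the predictor, so that "fixed effects were estimated to require 55 observations". Then: "To account for the random effects of clustering (students in the same classroom), a design effect of 1.82 was estimated". The inputs are a coefficient of variation of 0.15, "an average number of five students per classroom and a conservative Intraclass Correlation Coefficient value of 0.20". This gives 100 observations and, after 25% attrition, 134 students from 27 classrooms.

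**Analysis.** The student model under Data analysis has a random effect for classroom only. The Methods and analysis part of the abstract says that both school and classroom clustering will be accounted for.

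**The concern.** A design effect has to reflect the level at which units enter the arms. Here pupils in different classrooms of one school always share an arm, so anything that makes schools differ (age range, severity mix, timetable, staff culture) is carried whole into the comparison between arms. An inflation for classrooms alone treats 27 classrooms as if each had been allocated separately. It also leaves the test with the degrees of freedom of a trial of 55 independent observations (53), when the contrast between arms rests on six schools.

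Two things are at stake. If the school level is modelled, the trial may have much less power than stated for its primary outcome. If it is not modelled, as Data analysis is now worded, the test may reject a true null hypothesis more than 5% of the time.

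**Working it through.** **1. The plan's own figure.** A noncentral F test with one predictor, f² = 0.15 and two-sided α = 0.05 has power 0.805 at N = 55 and 0.798 at N = 54, so N = 55.

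- Design effect: DE = 1 + ((1 + CV²)m − 1)ρ = 1 + ((1 + 0.15²) × 5 − 1) × 0.20 = 1.8225.
- 55 × 1.82 = 100; 100 / 0.75 = 133.3, so 134; 134 / 5 = 26.8, so 27 classrooms.

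Every step reproduces.

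**2. The planned effect in SD.** For one balanced two-group predictor, d = 2√f² = 2√0.15 = 0.775.

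**3. Adding the school.** With 100 analysed pupils in 6 schools there are M = 100/6 = 16.67 per school. Reading 0.20 as the whole within-classroom correlation, including any school part:

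DE = 1.8225 + (16.67 − 5) × ρ_school; N_eff = 100/DE; noncentrality = 0.775 × √N_eff / 2.

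The document gives no school ICC, so the range is an assumption. So is the choice of 4 df (6 schools − 2; critical t 2.78, against 2.01 at 53 df).

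| School ICC | DE | N_eff | Power, 4 df | Power, df = N_eff − 2 | Detectable at 80% power, 4 df |
|---|---|---|---|---|---|
| 0 | 1.82 | 54.9 | 58% | 80% | 1.02 SD |
| 0.02 | 2.06 | 48.6 | 54% | 75% | 1.08 SD |
| 0.05 | 2.41 | 41.6 | 48% | 68% | 1.17 SD |
| 0.10 | 2.99 | 33.5 | 40% | 58% | 1.30 SD |

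The last column is 2 × 3.76 / √N_eff, where 3.76 is the noncentrality that gives 80% power with 4 df.

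**4. Sensitivity to class size.** If 100 analysed pupils are spread over 27 classrooms, there are 100/27 = 3.7 per class. The classroom DE is then 1 + (1.0225 × 3.7 − 1) × 0.20 = 1.56, and power with 4 df is 65%, 58%, 51% and 42% at the same four ICCs.

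**5. Sensitivity to the baseline measurement.** With a change score, the noncentrality is divided by √(2(1 − r)), where r is the within-student correlation. Assuming the same ICCs for change, DE as in step 3 and 4 df:

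| r | ICC 0 | 0.02 | 0.05 | 0.10 |
|---|---|---|---|---|
| 0.5 | 58% | 54% | 48% | 40% |
| 0.7 | 79% | 74% | 68% | 59% |
| 0.8 | 92% | 88% | 83% | 75% |

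With adjustment for baseline instead (divisor √(1 − r²)), the figures at school ICC 0.05 are 59%, 74% and 87% for r = 0.5, 0.7 and 0.8.

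**6. Type I error if only classrooms are modelled.** Approximately 2 × (1 − Φ(1.96 × √(1.8225/DE))). At school ICC 0.02, 0.05 and 0.10, the bracketed value is 1.85, 1.71 and 1.53, giving about 6.5%, 8.8% and 12.6% instead of 5%. This is a normal approximation for a comparison at one time point.

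**The case against.** Four points can fairly be made for the plan.

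- **Nothing is miscalculated.** This stands. A reader might infer an arithmetic error, but the printed chain is exact; the fault lies in the level of clustering chosen.
- **The 58% at school ICC 0 comes entirely from the choice of 4 df.** This stands too. The document fixes no method for degrees of freedom. With no school variance at all, classroom-level degrees of freedom (27 − 2 = 25) give 79%. But the document offers no ground for assuming zero, and the schools may be primary, secondary or combined and choose their own arm.
- **A small school ICC may already be absorbed.** With 3.7 analysed pupils per class, a school ICC of 0.02 gives DE = 1.56 + (16.67 − 3.7) × 0.02 = 1.82, which is the plan's own value. That disposes of the inflation at 0.02 but not at 0.05 or 0.10, nor of the degrees of freedom.
- **The planned model uses a baseline measurement.** This is the strongest point. A reader might infer that the trial is definitely underpowered, and the document does not support that: at r = 0.8 with 4 df, power passes 80% up to a school ICC of 0.05. But the sample size section states no correlation and claims no such gain; its only predictor is group.

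Nor do the documents say how a null result would be read, so no claim about that is made here.

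**Conclusion.** The point holds as a lack of support, not as proof of inadequate power. The effectiveness calculation accounts for classrooms while schools are allocated, so 80% power for 0.77 SD does not follow from what is printed. On the plan's own inputs, power is about 58% to 40% with 4 df, or about 75% to 58% with large-sample degrees of freedom once the school ICC is 0.02 to 0.10. These figures rest on an assumed school ICC, on the choice of degrees of freedom and on no gain from baseline; a high within-student correlation could restore much of the loss. That the school term is missing is certain; the percentages are conditional.

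The same gap appears in the analysis. The abstract commits to school and classroom clustering, but the student model names classrooms only. If schools differ, that model has type I error above 5%.

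**What to change.** 1. **Power paragraph.** Keep the sample. Restate power and the detectable difference, in SD and in MVPA minutes per day, over a range of school ICCs (for example 0.02, 0.05 and 0.10) with degrees of freedom suited to six schools. State any baseline to follow-up correlation relied on, with its source. Withdraw the unconditional 80% claim and present the effectiveness result as an estimate with a confidence interval.
2. **Student model under Data analysis.** Add the school level to agree with the abstract, and name a small-sample correction for the degrees of freedom. Because the effect of interest is group × time, the school term should let schools differ in their change; a school intercept alone would not do this.

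The cost is a rewritten paragraph and one amended model sentence, with no extra participants. The price is a less favourable power figure and wider intervals.

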### Timeline

The implementation trial will start in mid-2024 and participants will be able to enrol to the study up until the end of June 2025. Any school staff who registers after the end of June 2025 will not be invited to take part in surveys or interviews, as subsequent follow-up would exceed the implementation trial end date. The parallel effectiveness trial will be conducted for approximately 6 months (ie, 20 weeks); eligible schools will be able to register in the trial between mid-2024 and mid-2025 for a staggered and matched (intervention—wait-list control) start and a maximum duration of the trial not exceeding the end of 2025.

### Data analysis

Qualitative information collected from the interviews and focus groups will be analysed using thematic analysis^67^ in NVivo V.14 (released in 2023, Lumivero). Using a hybrid inductive/deductive approach,^68 69^ we will code data inductively and categorise codes in themes according to common implementation outcomes (ie, acceptability, adoption, feasibility, fidelity, penetration, sustainability and satisfaction).^57^ Where coded quotes do not apply to any of the preconcerted themes, new themes will be created.

Quantitative data will be analysed using Stata V.18 (Stata Corp. LLP). Preliminary analysis will be conducted to describe the sample (demographic characteristics and distribution of the scores on the outcomes of interest). Teacher-level outcomes from survey and EMA text message responses—including current teaching practices, organisational readiness/climate, teacher’s competence/confidence, and perceived barriers and facilitators in implementation, as well as frequency and types of *TransformUs All Abilities* strategies implemented by teachers (ie, EMA responses)—will be summarised descriptively. Changes over time in those outcomes’ scores will be analysed using linear mixed models. For teachers in the implementation trial, we will use time as a predictor variable (baseline/follow-up for survey scores; multiple time points for EMA). For teachers participating in the effectiveness trial, the predictor of interest will be the interaction between study group (intervention/control) and time. All models will be adjusted for common confounders (ie, teacher’s age, sex, years of teaching experience) and controlled for the random effect of classroom as a clustering variable.

Student-level primary and secondary effectiveness outcomes will be analysed using separate linear mixed models to assess the fixed effects of the intervention (ie, study group [intervention/control] × time [baseline/follow-up]) on each continuous outcome (ie, physical activity, sedentary time, sleep, physical literacy and cognitive functions), adjusting for common confounders (ie, age, sex and student disability/functioning) and controlling for the random effects of clustering (ie, students in classrooms). The effects of an interaction term between study group, time and student disability/functioning will also be explored, to see whether different levels of support moderate the intervention effects.

A person-centred analysis will also be explored as secondary analysis. Person-centred analyses involve creating groups of participants with similar characteristics or similar scores on the independent variables using a variety of techniques (eg, Cluster analysis; latent class analysis) to reduce the total variability.^70^ compared with variable-centred approach, this method has been suggested as a possible way of exploring how participants grouped by similar characteristics respond differently to the intervention in relation to the main outcomes of interest.^70^

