Estimating the exact percentage of school staff potentially registering for this initiative is challenging given the integrated nature of the *TransformUs All Abilities* programme within the *TransformUs* website (also including primary and secondary). The invitation for the implementation trial will only be made to school staff who indicate that they have children with disabilities in their class. According to the 2023 data from the Australian Bureau of Statistics,^58^ there were 9629 government/independent primary, secondary, combined and special schools in Australia. About 56% of the 3877 government/independent schools in the three States we intend to target for the implementation trial are potentially eligible to enrol in the trial (ie, n=2173 schools, including 208 special and 1965 mainstream schools). In 2023, there was a total of 167 107 teaching or specialist support school staff working in any government/independent schools in Victoria, Queensland and South Australia. Although the Australian Bureau of Statistics does not offer a breakdown of staff by school type,^58^ considering that the eligible schools represent 56% of the total number of schools in these States, the likely total number of staff eligible to enrol in the trial should not exceed 93 661 staff.

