### Sample size and power calculation

#### Implementation trial

Based on reach, we aim for at least 52 special schools (ie, 25% of the 208 eligible special schools) and 98 mainstream schools (ie, 5% of the eligible 1965 mainstream primary/secondary/combined schools) to uptake the *TransformUs All Abilities* programme.

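### The implementation-trial models list no school-type term, so if follow-up response differs between special and mainstream schools the single time effect can be biased, even as an average for the enrolled staff

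*Protocol article*

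**What the plan says.** The Data analysis section of the protocol article summarises staff survey and EMA outcomes descriptively and then models change with linear mixed models. For the implementation trial the stated predictor is time: "For teachers in the implementation trial, we will use time as a predictor variable (baseline/follow-up for survey scores; multiple time points for EMA"). The models are "adjusted for common confounders (ie, teacher’s age, sex, years of teaching experience"). On clustering, the article says they are "controlled for the random effect of classroom as a clustering variable". The covariate list opens with 'ie', so it reads as complete. School type is not a covariate, an interaction or a stratum.

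Elsewhere the article keeps the two settings apart:

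- **Sample size, implementation trial:** the first target is for special schools: "we aim for at least 52 special schools (ie, 25% of the 208 eligible special schools"). A separate mainstream target follows: "98 mainstream schools (ie, 5% of the eligible 1965 mainstream primary/secondary/combined schools"). Each counts schools that are "to uptake the *TransformUs All Abilities* programme".
- **Procedures and participants, implementation trial:** the eligible pool is "n=2173 schools, including 208 special and 1965 mainstream schools".
- **Study design:** staff of special schools are offered the trial as such. Mainstream staff are offered it if they report pupils with additional needs at registration. Victorian primary schools already registered for the original programme (714 schools, 2088 teachers) are also notified and invited.
- **Table 1:** in Queensland and South Australia, mainstream secondary staff are eligible and mainstream primary staff are not, so school type must be known to apply eligibility.

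**The concern.** A mixed model that uses all available responses gives a valid time effect under missing-at-random only if the variables that drive both loss to follow-up and the outcome are in the model. School type is a plausible variable of that kind. The two groups arrive by different routes and the expected uptake is 25% in one and 5% in the other. Part of the mainstream group may already use the original programme, which could affect both their starting level and their room to change.

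If special-school and mainstream staff answer the six-month survey at different rates, the follow-up sample has a different mix from the baseline sample. A model with no school-type term can read part of that shift as change over time. The EMA series is open to the same problem without any drop-out. Enrolment runs from mid-2024 to the end of June 2025 and messages are sought for up to six terms, so late registrants are likely to supply fewer of the later points. If enrolment timing differs by setting, the mix moves along the time axis.

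At stake are the estimated changes in staff confidence, barriers and strategy use, and whether a reader can see if the programme behaves alike in the two settings.

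**Working it through.** **1. The plan's own figures reproduce.** 0.25 × 208 = 52.0. 0.05 × 1965 = 98.25, stated as 98. 1175 + 237 + 553 = 1965, and 1965 + 208 = 2173. At target, special schools are 52/150 = 34.7% of schools.

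**2. Inputs the documents do not give.** Staff numbers, change, baseline difference and follow-up response by setting are all absent. The values below are assumptions. They take 160 special-school and 300 mainstream staff (34.8% special, close to 52:98), two time points, and a random intercept per staff member. This equals the stated classroom intercept only if each respondent has a separate classroom.

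**3. Formulas.** With n staff, response r and change d in special (s) and mainstream (m) schools:

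- Target for the enrolled mix = (n_s·d_s + n_m·d_m) / (n_s + n_m).
- When the baseline levels are equal, the time-only model estimates about (n_s·r_s·d_s + n_m·r_m·d_m) / (n_s·r_s + n_m·r_m).
- When baseline levels differ by B, it adds about (1 − ρ) × B × (special share at follow-up − special share at enrolment), where ρ is the within-person correlation.

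**4. Change and response both differ** (0.5 and 0.1; 70% and 40%). Responders: 160 × 0.7 = 112 and 300 × 0.4 = 120.

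- Target: (160 × 0.5 + 300 × 0.1)/460 = 110/460 = 0.239.
- Model: (112 × 0.5 + 120 × 0.1)/232 = 68/232 = 0.293.
- Excess: 0.054, or about 23% of the target.

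Simulating the random-intercept estimator (4000 runs at each ρ of 0.3, 0.5 and 0.7, with ρ treated as known) gave means of 0.291, 0.294 and 0.294, with Monte Carlo standard error about 0.001.

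**5. Milder inputs** (0.4 and 0.3; 60% and 50%). Responders: 96 and 150.

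- Target: (64 + 90)/460 = 0.335.
- Model: (38.4 + 45)/246 = 0.339.
- Excess: 0.004, or about 1%.

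**6. Equal change, unequal baseline** (change 0.3 in both, measured here in SD units; baseline difference 0.5 SD; 70% and 40%). The special share moves from 160/460 = 0.348 to 112/232 = 0.483. The added term is (1 − ρ) × 0.5 × 0.135: 0.047 at ρ = 0.3 and 0.020 at ρ = 0.7. The model therefore gives 0.32 to 0.35 against a true 0.30. The same simulation gave 0.349, 0.333 and 0.320. With the same baseline difference but 55% response in both settings it gave 0.300.

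**7. When nothing goes wrong.** If response does not differ by setting, the pooled effect equals the enrolled-mix average. If response differs but baseline level and change are both equal, the pooled effect is again right, and it then describes each setting too.

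**The case against.** The strongest case against acting has four parts.

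- **No conflict with the targets.** The 25% and 5% figures are uptake targets under reach, met or missed by counting schools. They set no target for change in scores. This stands. A reader might infer that modelling the settings together contradicts the separate targets, but the documents do not support that. The targets show only that the plan regards the settings as distinct.
- **The pooled average answers the stated objective.** The Introduction asks about implementation in schools overall and states no contrast between settings. This also stands. A reader might infer that a pooled slope describes neither setting, but that needs change to differ by setting, and no figure in the article shows that it does. Mainstream staff are invited only if they report pupils with additional needs, which narrows the contrast.
- **The magnitudes are assumed.** True. They range from about 1% to about 23% depending on the inputs, and the larger example is small in absolute terms (0.05) for constructs mostly built from 5-point items.
- **Subgroup terms and missing-data handling belong in an analysis plan.** This holds in part. An unseen plan may add the term, and descriptive summaries by setting are not ruled out. But the article does fix the model here. It states "All models will be adjusted for common confounders" and then gives a closed list without school type.

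State, school level or staff role could also modify change. School type has the better claim because the article itself recruits and sets targets by it.

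**Conclusion.** The point holds in conditional form. The listed implementation-trial model omits a known baseline variable by which the article recruits staff and sets its uptake targets. If follow-up response differs by setting, and baseline level or change differs too, the single time effect is not the average change of the enrolled staff. Equal change alone does not remove the problem, as step 6 shows; equal response does.

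The size cannot be fixed from the documents. Under the assumptions above it runs from negligible (0.339 against 0.335) to noticeable (0.293 against 0.239). The article gives no evidence that response, baseline or change will differ between settings, so this is a weakness in robustness and not a demonstrated bias. Nor do the documents support making the setting-specific estimates the main results; that would be a preference. Label: cheap improvement, minor to moderate.

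**What to change.** In the Data analysis section, add school type (special or mainstream) and school type × time to the implementation-trial models for survey and EMA outcomes. Report the estimated change in each setting alongside the overall change. Compute the overall change as the two setting-specific changes weighted by the numbers enrolled in each setting, not by the numbers who responded at follow-up.

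The cost is a sentence or two of text. Applying the eligibility criteria already requires school type to be known, so no new data collection is needed. The setting-specific estimates will have wider intervals than the pooled one, and there will be more estimates to report across the survey constructs.

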**Methods and analysis:**

This study employs a hybrid type II implementation-effectiveness trial to evaluate the *TransformUs All Abilities* programme, targeting all government and independent, primary and secondary schools in Victoria, as well as special and mainstream secondary schools in Queensland and South Australia (n=2173 eligible schools). The effectiveness trial will focus on a subgroup of government/independent special schools for students with mild to moderate intellectual disability in Victoria, involving up to three intervention and three waitlist control schools (n=61 eligible schools). In both trials, outcomes will be guided by the RE-AIM framework focusing on reach, adoption and implementation (implementation trial) and effectiveness (effectiveness trial), with data collected at baseline and 6 months. The effectiveness trial will focus on students’ device-measured physical activity and sedentary behaviour—primary outcomes—and sleep, physical literacy and cognitive functions—secondary outcomes. Teacher feedback on the programme’s adaptation and their experience with programme implementation will also be collected, alongside qualitative feedback from a subsample of students regarding engagement/enjoyment and suggestions for improvements. Implementation data will be analysed descriptively and using linear mixed models to test changes over time. Effectiveness outcomes will be analysed using linear mixed models to compare intervention and waitlist control, accounting for confounding and school/classroom clustering. Interview data will be thematically analysed.

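### As worded, the student models do not adjust the group × time effect for differential change by age, sex or functioning, although schools choose their arm

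*Protocol article*

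**What the plan says.** Under Recruitment strategy, the effectiveness trial is not randomised: "Allocation to intervention/wait-list control will be done pragmatically, based on schools’ preference".

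Under Data analysis, the student-level intervention effect is the term "study group [intervention/control] × time [baseline/follow-up"], estimated in a linear mixed model for each outcome, "adjusting for common confounders (ie, age, sex and student disability/functioning") and "controlling for the random effects of clustering (ie, students in classrooms"). No covariate × time term and no baseline-outcome adjustment is stated for this model. The only covariate interaction named is exploratory and concerns moderation: "The effects of an interaction term between study group, time and student disability/functioning will also be explored". For teachers in the effectiveness trial, likewise, "the predictor of interest will be the interaction between study group (intervention/control) and time", with adjustment for age, sex and teaching experience.

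The Abstract (Methods and analysis) describes the effectiveness analysis as "accounting for confounding and school/classroom clustering". The sample size section plans for 25% attrition in its calculation and mentions 30% drop-out and incomplete data in its text.

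**The concern.** With two time points, group × time is the difference between arms in within-student change. A covariate that is the same at both visits adds the same amount to both of a student's values, so it drops out of the change. To adjust a difference in change, the model must let change depend on the covariate, which takes a covariate × time term.

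This matters because the arms are self-selected. At most six schools take part. They may be primary, secondary or combined, and students may be 6 to 18 years old (Table 1). If arms differ in age or functioning, and students of different age or functioning would drift differently over about 20 weeks without the programme, that drift is counted as intervention effect. The list of confounders suggests protection against this, and on its ordinary reading it gives none.

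**Working it through.** **1. Algebra.** For student i with arm G, covariate X and random effects u (classroom, with or without student):

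- baseline: Y0 = a + bG + cX + u + e0
- follow-up: Y1 = a + bG + d + δG + cX + u + e1
- change: Y1 − Y0 = d + δG + (e1 − e0)

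The term cX has gone. With random intercepts and complete pairs, the mixed-model estimate of δ is the difference between arms in mean change, whatever c is.

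If change truly depends on X with slope θ, the expected estimate is δ + θ × (mean X in intervention − mean X in control). Adding X × time estimates θ and removes the second part.

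**2. Numerical check, complete data.** There were 300 simulated trials of 135 students in 27 classrooms of five (the protocol's classroom figures), with two visits and a true effect of 0. Assumed, because the protocol gives no values: arms differ by 0.6 SD in functioning, and change differs by −5 min/day per SD of functioning. The expected bias is −5 × 0.6 = −3.0 min/day.

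| Model | Mean group × time estimate (truth 0) |
|---|---|
| group × time only | −3.04 |
| plus age, sex, functioning as main effects | −3.04 |
| plus each covariate × time | −0.06 |

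The largest difference between the first two models in any trial was 0.0, with a classroom random effect only or with classroom and student. In one data set, recording age at each visit with a constant shift left the estimate at −7.435. Variable visit spacing moved it to −7.455, a shift of 0.02.

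**3. Numerical check, follow-up missing (about 25% when missing at random).** Same assumed confounding of change. Mean estimates, without covariates → main effects → covariate × time:

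| Missingness | Classroom and student random effects | Classroom only |
|---|---|---|
| completely random | −3.08 → −3.08 → −0.12 | −3.08 → −3.07 → −0.10 |
| depends on functioning | −2.45 → −2.72 → −0.14 | −2.20 → −2.76 → −0.08 |
| depends on functioning, opposite directions by arm | 0.53 → −0.95 → −0.07 | 1.70 → −1.37 → −0.06 |

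Main effects now move the estimate, because students with one visit contribute to it. They do not remove the confounding of change; covariate × time terms do.

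**4. Scale against the planned effect.** The plan's effect size is stated thus: "Assuming a moderate effect size (f² = 0.15"). One predictor, α = 0.05 and power 0.80 reproduce its 55 observations (power 0.805). For two equal groups this f² is d = 2 × √0.15 = 0.77 SD. Illustration with assumed inputs, where bias = age gap × slope of change on age:

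| Age gap between arms | Slope, SD per year | Bias | Share of 0.77 SD |
|---|---|---|---|
| any | 0 | 0 | 0% |
| 3 years | 0.05 | 0.15 SD | 0.15/0.77 = 19% |
| 5 years | 0.05 | 0.25 SD | 0.25/0.77 = 32% |

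Neither the gap nor the slope is in the protocol.

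**The case against.** **The article prints no model equation, and such detail often sits in the analysis plan.** True, and main effects only is an inference. But the article does state the effect term, the covariates and the purpose of the adjustment. Following that rule in the usual way gives an essentially unadjusted contrast of change. If covariate × time terms are intended, one sentence settles it.

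**A reader might infer that the adjustment does nothing at all.** The documents do not support that. The plan expects 25–30% loss, so complete pairs are not the planned situation. With missingness driven by functioning in opposite directions by arm, and functioning unrelated to change, main effects removed a bias of 1.07 min/day (classroom and student random effects) or 2.24 (classroom only). With a classroom-only random effect they can also alter the standard error (3.77 to 3.37 in one complete data set). This is useful work, but it is not control of confounded change.

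**A reader might also infer that the arms have no other protection.** That is too strong. Group × time removes stable differences in level, and restricting the trial to schools for mild to moderate intellectual disability limits the spread in functioning. An age range of 6–18 does not show that the arms will differ in age. On the other side, the matched start under Timeline is not described as matching on student characteristics.

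**The extra terms have a cost.** With at most six schools, a primary/secondary split between arms would make age nearly collinear with arm, and the adjusted effect would then lean on a linear extrapolation. This stands as a caution, not as a reason to leave change unadjusted.

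**Conclusion.** The point holds in this form: for students with both measurements, the adjustment as ordinarily read leaves the group × time estimate unchanged, and with loss to follow-up it acts only through the missing data. Differential change by age, sex or functioning between schools that chose their arm is therefore not addressed, and the abstract's statement on confounding promises more than the model delivers.

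The cancellation is algebra and rests only on two visits, random intercepts, complete pairs and covariates constant over the trial. The size of any bias is not known. The −3.04 min/day and the 19–32% of the planned effect follow from assumed imbalances and slopes, and a reader should not take them as the bias expected in this trial.

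For teachers the algebra is the same, but Table 1 expects only about 20 teachers and aides. The point carries little weight there.

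**What to change.** In Data analysis, state that the primary student mixed model contains group, time, group × time, age, sex and functioning, plus age × time, sex × time and functioning × time, with covariates taken at baseline, and that students with only one valid measurement stay in the model. Regressing each student's change on group and the covariates is equivalent only with complete pairs, because it drops those students. The exploratory three-way model does not replace this: it would normally contain functioning × time, but not age or sex by time. Fix the specification before the data are analysed.

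For the teacher models, use the same terms as a sensitivity analysis at most.

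Cost: a few degrees of freedom and no new data. In the complete-data simulations where functioning had no effect on change, the spread of the estimate rose from 2.40 to 2.59 min/day. Where it did have an effect, the spread was 2.57 against 2.59. The loss would be larger if age or functioning is strongly aligned with arm, so report the distribution of both by arm and school. Unmeasured differences between schools remain uncontrolled, and the abstract should claim adjustment for measured student characteristics only.
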